**Formative and Effectiveness Evaluation: Longer-term Outcomes**			
*All-Employee Survey*	Self-administered survey (paper and pencil) for all facility employees	• Self-rated health, body weight, health behaviors, perceived health needs, attitudes and beliefs • Symptoms of burnout and depression, history of injury and chronic disease • Location/severity of musculoskeletal symptoms, related functional impairment • Perceptions of working conditions, physical and psychological job features, organizational culture and climate • Knowledge of and perceived effectiveness of health and safety programs	Baseline & study end
*Organizational Readiness Survey*	SC members, DT co-facilitators, and union leaders: organization’s readiness to form participatory DTs and resources available to support the HWPP (45-item survey)	• Existing programs for safety, health, and well-being • Current program approaches for safety, health, and well-being • Current resources available for safety, health and wellbeing • Resources and readiness for change initiatives to improve safety, health and wellbeing • Resources and readiness for use of teams • Teamwork in work groups • Resources and readiness for employee participation • Management communication about safety, health, and well-being	Baseline & study end
*Leadership Interviews*	Scripted, open-ended interviews for SC members, DT co-facilitators, union leaders	• Perceived workforce safety and health concerns • Employee involvement^a^ in, successes of, and challenges to the existing safety program • Current strengths, opportunities, and obstacles to the HWPP within the facility • Shared DT/SC knowledge and understanding about root causes of safety and health concerns • Expected HWPP impact • Any unplanned consequences observed (negative or positive)	Baseline & study end
*Pre-Post Intervention Surveys*	DT-administered surveys	• Topic-specific measures based on key performance indicators (e.g., reduction of workplace exposures, short-term changes in behavior). Workforce sample determined by scope of intervention.	Pre- and post-IDEAS interventions

^a^primary outcome

**Fig. 2 Fig2:**
[figure not shown]
Logic model for the Healthy Workplace Participatory Program

#### Process evaluation

The HWPP relies on continuous participatory engagement of program participants and the workforce so that the workers’ own knowledge can inform customization of the program to local conditions, in keeping with the principles of participatory action research. Thus, a substantial amount of planned evaluation addresses the implementation process and corresponds to the Logic Model elements of “Activities and Outputs.”

Process evaluation addresses potential generalizability of the results by documenting specific conditions that necessitate customization as well as quantifying personnel and other resources needed for implementation. The choice of process measures is informed by implementation science research frameworks [59–61] with adaptations for the occupational safety and health setting [62]. For example, the level of participants’ engagement, enthusiasm and confidence in their roles is expected to predict the success of the program. Quality and usability of the program materials are also likely predictors. Characteristics of the implementation process include the participants’ efforts in planning, engaging, executing, reflecting, and evaluating the program steps. External forces and organizational characteristics of the study sites may either facilitate or impede program implementation.

Process measures registered as *primary outcomes for this clinical trial* are team attendance, team engagement, level of committee activity, and scope of health, safety, and well-being issues addressed. Process measures registered as *secondary outcomes* include proportion of the HWPP protocol and content followed (fidelity), and development of shared labor-management awareness of job-related health issues.

#### Formative evaluation

Pre-program data on workforce health, safety, and well-being provide baseline assessments of potential problems to be addressed. Workers’ compensation (WC) and administrative data are collected retrospectively at baseline to provide context and understanding of major health and safety needs. Each site will provide de-identified electronic administrative data files annually covering workforce size and demographics; employee retention by job group; workers’ health-related absenteeism, and WC claims and costs. These data will also be collected prospectively over the course of the study.

The baseline All-Employee Survey (AES) assesses the starting conditions for individual-level employee health status, burnout, and work ability; frequency of threats, assault, and harassment of employees; staff-reported quality of care of patients/residents; and perceived organizational support for workforce health, safety, and wellbeing.

Baseline interviews with upper and mid-level managers, as well as union leaders, assess perceptions of priority employee safety and health concerns, alignment of the HWPP with organizational goals, as well as expectancies for program outcomes and sustainability. (The interview guide was developed for this study (see Supplementary File). Organizational readiness surveys of the same organizational leaders assess perception in organizational resources and readiness for safety and health programs, teamwork and communication, and organizational-level readiness for worker participation in program design. These domains are associated with successful implementation of participatory ergonomics programs and safety-related organization change efforts [63]. Baseline data from organizational leaders will identify training needs and other possible resource gaps to address for successful implementation of the HWPP. Follow-up data will be gathered through regular interviews and surveys of the same managers, program champions, and union leaders, as well as DT members.

#### Effectiveness evaluation

Effectiveness outcome measures include changes in the formative measures over time, designated in the Logic Model as “Short Term,” “Intermediate,” and “Long Term” outcomes (Fig. 2). Short-term outcomes include changes in knowledge and skills of Design Team members (e.g. greater awareness of perspectives of other employees in different work units and at different levels of the organizational hierarchy, increased quality of communication and level of engagement, and focus on safety, health, and well-being concerns of employees), as well as management commitment of resources for implementing safety/well-being interventions.

At the facility level, the goal is that locally-designed interventions on DT-selected topics will be implemented through the authority of the Steering Committee. Their eventual effectiveness on relevant metrics of organizational performance will be assessed at multiple levels. We expect the training provided to teams to result in the production of intervention ideas that reflect both work and non-work contributors. Therefore, the team-generated interventions will be assessed for TWH characteristics.

Organizational performance will be assessed through interim interviews of champions, co-facilitators, and organizational leaders to assess expectancies related to implementation and impact of interventions selected by the Design Team. A survey will be administered to DT members semi-annually to collect similar measures, plus measures of personal involvement, program value, and management support.

Longer-term effectiveness analyses will utilize data from the AES, administered at least twice during the study. Outcomes of interest include changes in workers’ exposures, stressors, work climate, and perceived organizational support, as well as individual-level health, safety, and wellbeing (Table 1). Organizational readiness surveys will be re-administered with organizational leaders to assess changes in resources and readiness for participation, change initiatives, safety and health teamwork and communication.

While valuable for tracking large trends in a workforce, the AES may not be sensitive to specific interventions, especially if these target certain units or workforce sub-groups. The IDEAS toolkit calls for the DT to identify measurable key performance indicators for each intervention. The DT will use these to generate topic-specific measures such as pre/post “mini-surveys” to assess impact in the appropriate segment(s) of the workforce. The HWPP intervention includes investigator coaching on how to design and conduct targeted pre/post surveys. Thus, carrying out these targeted surveys will itself be recorded as a measure of committee effectiveness. If different DT’s select the same issue during the study, the investigators will suggest use of overlapping measures, to facilitate cross-facility comparison and pooling of data on effectiveness.

### Data analysis

#### Process evaluation

Short-term process measures will be summarized for each committee over time and compared between the control and intervention groups. For example, changes in implementation metrics will quantify the extent to which the participatory DTs utilized the HWPP program (uptake) and adhered to it (fidelity, sustainability). The DT surveys and Coach notes will be summarized to document the development of team functionality, independence, ability to plan and implement activities, and ability to evaluate success or setbacks of activities to improve the process in the future. We will also describe obstacles and opportunities in each setting, and the extent to which these are similar among agencies.

We will summarize the accomplishments of the HWPP and the factors observed to affect implementation and outcomes of the program; the challenges and successes of long-term team maintenance; and how these were different from or similar to the challenges and successes of the health and safety committees in the control sites before the lagged interventions. We will discuss the implications of these combined qualitative and quantitative findings for potential long-term sustainability of the participatory programs. These findings may be relevant to post-hoc analyses of any site differences in effectiveness and will also inform future refinements in HWPP content or delivery.

#### Formative evaluation

Initial analyses of individual-level AES data will quantify the baseline magnitude of worker health and health-related indicators, such as burnout/depression, musculoskeletal symptoms and function, recent assault, and acute injury. Data will be summarized by study group (immediate/lagged intervention), facility, and job group. Cross-sectional associations with work environment features will focus on dependent variables prioritized by DT and SC members in the initial surveys and interviews. Candidate job characteristics are physical and psychosocial job demands, decision latitude, perceived supervisor and coworker support, and work schedule.

We will also generate descriptive data on institutional characteristics such as average ratings of organizational culture and climate; quality of safe patient/resident handling and other worker health or safety programs; compensation claim rates; employee turnover rates; and clinical staffing ratios. These analyses will be done by site for customized reports, and by agency type and study group to assess potential confounding and effect modification.

#### Effectiveness evaluation

The pre/post “mini-surveys” will be analyzed to assess short-term effectiveness of locally-designed interventions within the proportion of the workforce expected to benefit. Employee participation in DT-promoted activities will be compared between study groups and over time (pre- vs post-intervention).

Organizational-level improvements in worker engagement, communication or shared understanding between management and workforce, SC authorization of resources, or uptake and institutionalization of new practices will be interpreted as effectiveness of the participatory intervention process, at the overall study level.

Assuming that both groups intervene on similar topics over time, pooled effectiveness analyses will compare AES data in the immediate intervention and lagged intervention groups. If sufficient numbers of workers complete more than two surveys, we will also use a difference-in-difference approach. Reporting of individual-level outcomes (e.g., changes in occupational exposures, health beliefs and behaviors) will follow the CONSORT guidelines for cluster randomized trials [64].

Statistical power calculations for intention-to-treat comparisons of several key outcomes (Table 2) were conducted for difference-in-difference analysis, with two-sample differences at the population level. The facilities within each pair are of different workforce sizes, so we assumed conservatively the smaller of the facilities from each pair in both groups. Full-time equivalent denominators were assumed to represent 90% of headcount; a 75% response rate gave samples of about 1650 workers per group. We used a binomial distribution for proportions (e.g., smoking) and Gaussian distribution for means (e.g., body mass index (BMI)). Starting values were taken as those found in our prior healthcare study using a similar instrument [31, 32, 65]. Modest differences should be readily detectable, assuming facility-wide implementation of each HWPP intervention.

**Table 2 Tab2:** Smallest detectable differences in selected outcomes with 80% power (alpha = 0.05, two-sided *p*-value)

Outcome	Baseline value	Detectable difference
Injury rate	0.71 / FTE	.062 / FTE
Smoking	Prevalence 25.6%	6.0%
BMI	Z = 28, SD = 9	0.9
Health self-efficacy	Z = 27, SD = 8.5	0.8
Work ability	Z = 8.9, SD = 2	0.19

In addition, where interventions have addressed health outcomes that are generally attributed to working conditions, workers’ compensation claims will be compared over time. For example, with an occupational safety and health intervention such as installation of safe patient handling equipment, benefits may be measured through change in WC claim rates and costs for back injuries and muscle strains.

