### Methodologic considerations

Although workplace integration of programs in occupational health and health promotion seems desirable, there are challenges. One is that integrated programs require more time, effort, and commitment from the organization [67]. For example, we expect the management steering committee to provide timely constructive feedback to interventions proposed by the DT, as well as financial and organizational resources for implementing and evaluating them. The biggest barrier to front-line employee participation in a previous healthcare program was lack of release time for employees [68]. Although obtaining such commitment from the organization takes time and effort, we believe it will be worthwhile because organization culture, environment, and leadership support are closely associated with employee safety and health [32, 69].

The standardized All-Employee Survey will be valuable for tracking large trends in the study population, but if the intervention only benefits a sub-group, any effect could be diluted and difficult to observe. Further, individual health outcomes, as well as workplace culture and organizational features, may evolve gradually enough that there is not adequate time to see changes. We have included a number of proximal endpoints to alleviate this potential challenge. For example, perceived management support of safety relates to longer-term outcomes HWPP, through the multi-level communication and organizational learning that results from the IDEAS process.

Because of the high degree of participatory decision-making, specific health targets selected may vary among DTs. The facilities have generally indicated a similar set of concerns, but even if intervention topics overlap across the sites, they will not necessarily be taken up in the same sequence. This requires that we examine both generic injury/illness outcomes, as well as problem-specific outcomes. Depending on the sequence in which the same topics are addressed in each facility, the length of follow-up time for those endpoints may vary and need to be adjusted for accordingly.

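### The All-Employee Survey analysis that was powered, a difference-in-difference, is only an optional extra whose condition cannot be met on the two-wave schedule, and the comparison that remains depends on topics chosen after randomisation

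*Protocol article*

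**What the plan says.** Under Data analysis, Effectiveness evaluation, the protocol article introduces the AES comparison with a condition: "Assuming that both groups intervene on similar topics over time, pooled effectiveness analyses will compare AES data" between the immediate and lagged groups. The next sentence adds a second analysis with its own condition: "If sufficient numbers of workers complete more than two surveys, we will also use a difference-in-difference approach".

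The paragraph after that reports power: "Statistical power calculations for intention-to-treat comparisons of several key outcomes (Table 2) were conducted for difference-in-difference analysis". These are two-sample differences at population level with about 1650 workers per group. Table 2 gives detectable differences at 80% power for injury rate, smoking, BMI, health self-efficacy and work ability.

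The AES row of Table 1 sets the schedule as "Baseline & study end". The earlier Effectiveness evaluation section, under Evaluation, treats two administrations as a minimum. Under Intervention protocol, each site's Design Team and Steering Committee choose the topics. Methodologic considerations notes that topics and their sequence may differ and concludes: "This requires that we examine both generic injury/illness outcomes, as well as problem-specific outcomes".

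**The concern.** The analysis used for power and the analysis planned by default are different. The first depends on a condition that has nothing to do with what a difference-in-difference requires. One measurement before and one after is enough. The population-level form named in the power paragraph compares group means at each wave, so the same workers need not answer twice, let alone three times.

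The remaining comparison rests on an assumption about what the teams will do after randomisation. Lagged sites start the coached process only part-way through, so during the control period they have no programme topics to match. Deciding whether to pool according to later choices lets those choices determine whether an AES effect estimate is reported. That is hard to square with the intention-to-treat description in the power paragraph.

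At stake is whether the AES effectiveness result comes from a fixed analysis with known power. With so few facilities, the article itself concedes that randomisation will not reliably prevent confounding, so an analysis that uses the baseline wave is the natural default.

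**Working it through.** **Schedule against condition.** Table 1 lists two AES waves, so the most surveys a worker can complete is two. The condition asks for more than two, so the number of workers who can qualify on that schedule is zero. It becomes positive only if a third wave is added, which the minimum-of-two wording allows.

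**Which analysis Table 2 represents.** Inputs from the power paragraph and Table 2: two-sided alpha 0.05, power 80%, n = 1650 per group ("a 75% response rate gave samples of about 1650 workers per group"), and the baseline values and SDs. The multiplier is 1.960 + 0.842 = 2.802. Workers are treated as independent, with no allowance for clustering.

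- Single two-sample comparison: detectable difference = 2.802 × √(2 × variance / n)
- Difference-in-difference on four independent samples: 2.802 × √(4 × variance / n)

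| Outcome | Table 2 | Single comparison | Four-sample difference-in-difference |
|---|---|---|---|
| Smoking, 25.6% | 6.0 points | 4.1 to 4.4 | 6.02 |
| Injury, 0.71/FTE (binomial variance) | 0.062 | 0.044 | 0.0626 |
| BMI, SD 9 | 0.9 | 0.878 | 1.24 |
| Health self-efficacy, SD 8.5 | 0.8 | 0.829 | 1.17 |
| Work ability, SD 2 | 0.19 | 0.195 | 0.276 |

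Examples:
- Smoking, four-sample: 2.802 × √(4 × 0.256 × 0.744 / 1650) = 0.0602.
- BMI, single: 2.802 × 9 × √(2/1650) = 0.878.
- BMI, four-sample: 2.802 × 9 × √(4/1650) = 1.24.

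The smoking range covers a decrease (4.1) and an increase (4.4). Injury reproduces only if the rate is given binomial variance, 0.71 × 0.29. Poisson variance gives 0.082 for a single comparison and 0.116 for the four-sample form. Work ability matches 0.19 only by truncation.

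So the table reproduces to about its displayed precision, but with different formulas: the two rates follow the four-sample difference-in-difference and the three means follow a single comparison.

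**An alternative reading of the means.** If the same workers are measured twice with correlation ρ, the variance term is 4 × variance × (1 − ρ) / n. At ρ = 0.5 this equals the single-comparison formula, so it also returns 0.878, 0.829 and 0.195. The documents state no correlation. For BMI the detectable difference runs from 1.04 at ρ = 0.3 to 0.56 at ρ = 0.8.

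**Power if the four-sample form is run.** Power = Φ(d / SE − 1.960).
- BMI: SE = 9 × √(4/1650) = 0.443; 0.9/0.443 − 1.960 = 0.07; power 53%.
- Health self-efficacy: SE = 0.419; power 48%.
- Work ability: SE = 0.0985; power 49%.
- Smoking: SE = 0.0215; power 80%.

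The figure of 1650 cannot be rebuilt, because facility headcounts are not given.

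**The case against.** Several stronger readings are tempting, and the article does not support them.

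- *The powered analysis will never be run.* A reader might infer this from Table 1 alone. The Evaluation text makes two waves a minimum, so a third could be collected. The pooled comparison may also go ahead, since Methodologic considerations reports broadly similar concerns across facilities.
- *The default is an unadjusted follow-up comparison, so baseline imbalance passes straight into the estimate.* The article does not say this. It describes effectiveness outcomes as changes over time, and Methodologic considerations plans to compare groups at baseline and adjust for differences. Finer modelling detail may be in an analysis plan that is not shown.
- *The trial's main answer depends on topic choice.* The registered primary outcomes are process measures: attendance, engagement, committee activity and scope of issues. No AES item carries the primary-outcome mark in Table 1.
- *The topic problem is ignored.* The article discloses it and intends to examine generic outcomes too. If the pooled comparison is run, it still compares the groups as assigned.

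These points limit the consequences. They do not remove the contradiction: the survey-count condition is wrong for the method, it cannot be met on the stated schedule, and the section that sets out the pooled AES comparison frees no outcome from the topic assumption.

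**Conclusion.** The point holds as an inconsistency in the longer-term AES effectiveness analysis. The analysis that was powered is not the unconditional planned one, and it is unavailable on the schedule in Table 1. The comparison that remains is conditional on choices made after randomisation.

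Table 2 does not settle which analysis was meant, because its rates and means rest on different formulas. If a four-sample difference-in-difference is run, detectable differences in the three means rise by a factor of √2 over the single-comparison values (BMI from 0.878 to 1.24), with power of about 48% to 53% at the stated differences. If a single comparison is run instead, the smoking entry is conservative (4.1 to 4.4 points against 6.0). These figures assume 1650 independent workers per group at each wave.

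**What to change.** 1. Delete the condition on the number of surveys completed.
2. Make a group-by-period difference-in-difference the unconditional AES effectiveness analysis, using all respondents at each wave, with facility terms and agency pair as stratum. Apply it to named generic outcomes, such as work ability, injury rate and perceived management support, whatever topics the teams choose. Because one facility has withdrawn, say how its unpaired partner enters.
3. Keep linked workers as a sensitivity analysis and topic-matched comparisons as secondary.
4. State which waves are used. With baseline and study end only, both groups have been coached by the second wave, so the contrast is earlier versus later intervention and should be described that way. If a wave before crossover is collected, as the text allows, use it for the intervention-versus-control contrast.
5. Recompute Table 2 with one formula for the analysis to be run, stating any within-worker correlation and the variance used for injury.

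The cost is wording and recalculation, since baseline and study-end data are already planned. A wave before crossover is not in Table 1 and would mean another all-employee survey. Generic outcomes may dilute topic-specific effects, and some detectable differences may become less favourable.

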Job stress and burnout are high among healthcare workers and associated with both psychological and somatic distress [27–29]. Psychosocial stressors, night work, and workplace assault are associated with chronic disease risk factors such as smoking, physical inactivity, obesity, sleep, and mental wellbeing [30–32], health concerns that are not typically attributed to work. Psychosocial stressors have also been linked to high staff turnover intention in nursing homes [32]. Healthcare institutions face substantial challenges in retaining direct care personnel due to workplace health and safety issues. Annual turnover rates for registered nurses are estimated to range from 18 to 26% [33], with cost estimates for each turnover ranging from $62,100–$67,000 [34]. High personnel turnover impacts organizational conditions that increase workplace hazards, creating a vicious cycle and posing challenges for patient safety and quality of care.

This multiplicity of hazards and outcomes poses practical challenges for employee health champions. It can be difficult to prioritize efforts, especially when there is insufficient understanding about how exposures interact with each other, how to interrupt the positive feedback loops, and whether there are common barriers to improving working conditions in these various domains. There is an emerging agreement that workplace health interventions should operate at multiple levels of influence [35], and that health and safety interventions should address work organization and empowering employees in problem identification and resolution [36, 37]. However, there is limited experience with a systematic approach to identify and address the interplay among this myriad of causal factors in order to improve healthcare worker mental and physical health effectively [29, 38, 39].

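### Table 2 is described as one difference-in-difference calculation, but the smoking row and the three continuous rows rest on different bases

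*Protocol article*

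**What the plan says.** The power text and Table 2 are in the data analysis part of the protocol article, under Effectiveness evaluation. The calculations "were conducted for difference-in-difference analysis, with two-sample differences at the population level". On sample size, "a 75% response rate gave samples of about 1650 workers per group". The table title reads "Smallest detectable differences in selected outcomes with 80% power (alpha = 0.05, two-sided". One method is described for every row, and only the distribution changes: binomial for proportions, Gaussian for means.

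The entries at issue are:
- smoking, "Prevalence 25.6" per cent at baseline, detectable difference 6.0%
- BMI, mean 28, SD 9, detectable difference 0.9
- health self-efficacy, mean 27, SD 8.5, detectable difference 0.8
- work ability, mean 8.9, SD 2, detectable difference 0.19

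The SDs are listed as baseline values. No within-worker correlation and no SD of change is given. The text then concludes that modest differences should be easy to detect if each intervention is implemented facility-wide.

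**The concern.** A difference-in-difference compares two changes. With unlinked samples at each wave, its variance contains four group means, against two for a comparison at one time, so the detectable difference is larger by the square root of 2. A table said to rest on one method should carry the same factor in every row. Here the smoking row carries the four-mean factor and the three Gaussian rows carry the two-mean factor.

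The rows therefore cannot be compared with each other. If independent cross-sections were meant, which is the plain reading of a population-level calculation, the three continuous rows are too optimistic. They also help support the statement that modest differences are easy to detect.

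**Working it through.** **Inputs, all from the power text and Table 2.** n = 1650 per group; two-sided alpha 0.05; power 80%; the SDs and prevalence listed above. The multiplier is k = 1.960 + 0.842 = 2.802. For a proportion, SD = sqrt(p(1 − p)); for smoking, sqrt(0.256 × 0.744) = 0.436.

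**Formulas.**
- A, two groups at one time: k × SD × sqrt(2/n), with k × sqrt(2/1650) = 0.0975.
- B, difference-in-difference of four independent samples: k × SD × sqrt(4/n), with k × sqrt(4/1650) = 0.1379.
- C, difference in change scores of linked workers with correlation rho: k × SD × sqrt(2(1 − rho)) × sqrt(2/n). This equals B at rho = 0 and A at rho = 0.5.

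**Reproducing the table.**

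| Row | Stated | A | B | rho that makes C equal the stated value |
|---|---|---|---|---|
| Smoking | 6.0% | 4.26% | 6.02% | 0.01 |
| BMI | 0.9 | 0.878 | 1.24 | 0.47 |
| Health self-efficacy | 0.8 | 0.829 | 1.17 | 0.53 |
| Work ability | 0.19 | 0.195 | 0.276 | 0.53 |

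The last column is rho = 1 − (d/(k × SD))² × n/4. For BMI: 1 − (0.9/25.21)² × 412.5 = 0.47.

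**Can rounding explain the split?** The group sizes that would round to the stated differences are:

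| Row | n under A | n under B |
|---|---|---|
| BMI | 1409–1760 | 2818–3520 |
| Health self-efficacy | 1570–2017 | 3140–4033 |
| Work ability | 1652–1835 | 3303–3670 |

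About 1650 fits A in all three rows, with work ability at the edge, and B in none. Smoking behaves the other way. B implies n = 1661, while a single-time comparison would need only 762 (decrease) or 890 (increase) per group for 6 points.

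**Injury row.** If 0.71 per FTE is treated as a binomial proportion, B gives 0.0626 against the stated 0.062, and A gives 0.044. That treatment is an assumption, and the conclusion does not rest on it.

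**Power at the tabulated differences under B.** Power = Φ(d/(SD × sqrt(4/n)) − 1.960), with sqrt(4/1650) = 0.0492:
- BMI: 0.9/0.443 = 2.031, power 53%
- Health self-efficacy: 0.8/0.4185 = 1.912, power 48%
- Work ability: 0.19/0.0985 = 1.929, power 49%

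**Sensitivity to correlation.** In a fully linked cohort of 1650 per group, the detectable BMI difference is 1.24 at rho 0, 1.04 at 0.3, 0.88 at 0.5 and 0.68 at 0.7.

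**The case against.** The strongest reply is that the arithmetic cannot tell a single-time comparison from a linked change-score analysis with rho near 0.5. The article gives some support for linkage. It says "If sufficient numbers of workers complete more than two surveys, we will also use a difference-in-difference approach", and the human subjects section collects identifiers for linking records across stages. This stands: the factor of 1.4 and the power near 50% are conditional on independent cross-sections. It does not rescue the table, because no correlation is stated and the smoking row would still imply a correlation near zero.

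Two stronger readings are tempting, and the documents support neither.

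- **A reader might infer that a linked cohort is out of reach**, because the Background says "Annual turnover rates for registered nurses are estimated to range from 18 to 26" per cent. Take 1650/0.75 = 2200 workers, 75% response independently at both waves and that turnover for all staff. Then 2200 × 0.75² × 0.82^1.5 = 919 remain linked per group at 18% over 1.5 years, and 2200 × 0.75² × 0.74³ = 501 at 26% over 3 years. But the rate is a cited estimate for registered nurses, not for all job groups at these sites, and 3 years is an assumed interval. Fewer linked workers can also be offset by correlation: BMI 0.9 is reached at rho 0.71 with n = 919 and at rho 0.84 with n = 501. The article gives no correlation, so it does not settle the matter.
- **A reader might infer that the 1.4 factor simply multiplies any inflation for clustering by facility.** Stable facility effects cancel in a difference-in-difference but not in a single-time comparison. As an illustration only, assume three facilities of 550 per group, an intraclass correlation of 0.01 and normal quantiles. The BMI figure is then 2.24 at a single time. As a difference-in-difference it is 3.16, 2.40 or 1.79 at a between-wave facility correlation of 0, 0.5 or 0.8. The ratio can fall below 1.

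It can also be said that the main pooled survey comparison is between groups, with difference-in-difference only an addition, so labelling each row would be enough. Labels would cure the ambiguity, but the sentence describing one difference-in-difference method would still have to change.

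**Conclusion.** Table 2 does not rest on the single basis the text describes. That finding needs only the article's own inputs and holds whether or not workers are linked. The size depends on the reading. With independent cross-sections of 1650 per group per wave and no clustering, the detectable differences are 1.24, 1.17 and 0.28, and power at the tabulated values is about 53%, 48% and 49%. With full linkage and rho near 0.5, the three continuous figures stand and smoking is the row out of line.

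A reader might take this as a threat to the trial's main conclusions. The documents do not support that. The registered primary outcomes are attendance, engagement, committee activity and scope of issues, none of which is in Table 2, and the Discussion attributes the small number of sites to resources. What is affected is the published power statement for individual-level effectiveness outcomes.

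**What to change.** Recompute every row on one stated basis and name it in the text and the table.

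- **Repeated cross-sections:** BMI 1.24, health self-efficacy 1.17 and work ability 0.28, with smoking unchanged at 6.0%. These are before any allowance for clustering, and before the facility withdrawal reported under Study revisions after the start date. That withdrawal leaves two lagged sites, whereas 1650 per group counts one facility from each of three pairs.
- **Linked cohort:** state the assumed within-worker correlation and the expected number linked per group, show the detectable differences over a range of both, and recompute smoking in the same way.

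Derive any clustering allowance for the chosen design rather than multiplying it on. State how the injury rate was modelled. Then reword the sentence on how easily modest differences can be detected to match the new figures.

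The cost is a short recalculation and a few edited sentences. On the cross-sectional basis, three published figures become less favourable. No change to enrolment, conduct or the registered primary outcomes follows.
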